#### Sustainability

Sustainability of TASSH will be evaluated 6 months after the completion of the PF implementation interval. Sustainability will be defined in the same manner as adoption and classified using two 3-month intervals during the follow-up measurement period lasting 6 months. Rates of sustainability will be represented using descriptive statistics (rates of sustainability overall and by clinic). Levels of sustainability over time will be represented with descriptive tables. We will compare sustainability of TASSH to adoption in the intervention interval through descriptive summaries across sites. To examine whether sustainability changes over time, we will use a GLMM to assess the effect of time on sustainability. Specifying a main effect of time with sustainability as our outcome, we will interpret a main effect of negative magnitude to indicate that rates of sustainability decrease over time. We hypothesize that sustainability will not decline over time. Potential covariates and confounding factors which may influence levels of sustainability will be identified and may be included in adjusted analyses, if possible, due to limited degrees of freedom for the sites/clusters.

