**Design:**

In partnership with the Nigerian Federal Ministry of Health (FMOH) and community organizations, the MAP-IT trial takes place in 30 PHCs. The i-PARiHS framework guided pre-implementation needs assessment. The RE-AIM framework will guide post-implementation activities to evaluate the effect of practice facilitation on the adoption, implementation fidelity, and sustainability of a hypertension program, as well as blood pressure (BP) control. Using a SW-CRT design, PHCs sequentially crossover from the hypertension program only (usual care) to hypertension plus practice facilitation (experimental condition). PHCs will recruit and enroll an average of 28–32 patients to reach a maximum of 960 PLWH participants with uncontrolled hypertension who will be followed longitudinally for BP outcomes.

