**Fig. 2 Fig2:**
[figure not shown]
Stepped wedge study design

Nurses at these PHCs will implement all aspects of TASSH in their clinical care for PLWH with uncontrolled hypertension. PFs will support nurses during the 12-month period by helping with hypertension treatment issues and addressing barriers to TASSH implementation. The RE-AIM framework defines measures to evaluate the effect of PF on TASSH adoption after 12 months of PF compared to TASSH adoption without PF (primary outcome). RE-AIM facilitates evaluation of the effect of PF on BP control (secondary outcome) and the level of TASSH implementation fidelity (secondary outcome).

Following each cohort’s 12-month implementation phase, each PHC transitions to the post-implementation phase (follow-up period). Nurses will continue to implement TASSH. However, PF will end. Six months into this post-implementation period (18 months following the start of PF), we will evaluate the sustainability of TASSH within the PHCs (secondary outcome). Figure 3 provides an overview of the study design including the pre-implementation, implementation, and post-implementation phases.

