### Secondary outcomes

Secondary outcomes include BP control, implementation fidelity, and TASSH sustainability. BP control is defined as a BP less than 140/90 mm Hg. For those consented and enrolled, at baseline visit, three BP readings will be taken by nurses using an automated BP monitor with the participant seated comfortably for 5 min prior to the measurements, following standard guidelines. The average of the latter two BP readings will be used as the measure for each visit. The same procedure will be followed for each participant visit, including the 12-month visit. Uncontrolled BP is defined by an average clinic systolic *BP* ≥ 140 mm Hg or diastolic *BP* ≥ 90 mm Hg following the guidelines set forth by WHO for CVD treatment [31, 32] and in accordance with the Nigeria Hypertension Treatment Protocol.

Fidelity to TASSH will be measured throughout the study and defined by five dimensions: (1) adherence to the program protocol, (2) dose of the program delivered, (3) quality of program delivery, (4) participant responsiveness, and (5) program differentiation. Tools to assess fidelity were developed for this study and adapted from the current literature [39–41]. Fidelity measures will evaluate adherence from the perspective of the PF, nurses, and the participants.

Sustainability is defined as the maintenance of TASSH adoption at HIV clinics at 18 months (6 months after the end of each cohort’s TASSH + PF phase). Sustainability will be assessed similarly to adoption (as defined above) and qualitatively, based on interviews with nurses and clinic leadership at 18 months. The research coordinator will conduct the interviews with two nurses and one key leadership personnel at each clinic. The interviews will be guided by i-PARiHS and inquire about attitudes regarding TASSH implementation, barriers, facilitators, and implications for scalability. All interviews will be recorded, transcribed, and analyzed with NVivo Version 11.

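### The formal sustainability analysis looks only within the six months after practice facilitation ends, so adoption lost at withdrawal gets no model-based estimate or test

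*Protocol article*

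**What the plan says.** Under Secondary outcomes, the protocol article gives the definition: "Sustainability is defined as the maintenance of TASSH adoption at HIV clinics at 18 months". The 18 months run from the start of PF, so the time point lies six months after each cohort's PF phase. Of the post-implementation period, the Study design section says: "However, PF will end".

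The Sustainability paragraph of the secondary analyses sets the outcome window: "Sustainability will be defined in the same manner as adoption and classified using two 3-month intervals during the follow-up measurement period lasting 6 months". It then names one model: "To examine whether sustainability changes over time, we will use a GLMM to assess the effect of time on sustainability". The reading rule begins "Specifying a main effect of time with sustainability as our outcome, we will interpret a main effect of negative magnitude" and treats such an effect as a fall in sustainability. The hypothesis is: "We hypothesize that sustainability will not decline over time".

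The PF period enters in one sentence: "We will compare sustainability of TASSH to adoption in the intervention interval through descriptive summaries across sites".

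The abstract says RE-AIM will guide activities to "evaluate the effect of practice facilitation on the adoption, implementation fidelity, and sustainability of a hypertension program".

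**The concern.** Maintenance needs a reference level. The natural one here is the adoption reached by the end of PF, in months 10-12. The planned time effect does not use it. Both follow-up intervals, months 13-15 and 16-18, lie after PF has stopped, so their difference measures only whether adoption keeps drifting once support is gone.

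If support matters, the obvious place for a loss is the step from month 12 to month 13, which lies outside the model. Adoption could fall back to its usual-care level at that step and the formal result would still agree with the stated hypothesis. The size of the loss, which answers the question set by the definition, would appear only as unadjusted summaries. It would have no interval and no allowance for calendar time, although the Limitations section names temporal trends as a notable limitation of the design.

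**Working it through.** **What each model covers**

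| Analysis in the article | Periods covered | Spans the end of PF? |
|---|---|---|
| Primary GLMM (Primary outcomes analyses; Sensitivity analysis) | usual care and PF | no |
| Time effect on adoption (Primary outcomes analyses) | four PF quarters | no |
| Time effect on sustainability (Sustainability) | two post-PF quarters | no |
| Descriptive comparison (Sustainability) | PF and post-PF | yes, without a model |

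Modelling months instead of quarters would not change this, because every time point of the sustainability outcome would still follow PF.

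**Size of the consequence**

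The article gives no power or margin for sustainability, so there is no stated figure to reproduce.

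Inputs from the article: 30 PHCs; two-sided 5% level; PF gains of 15 to 20 points in Table 2. The ICC of 0.05 lies in the 0.02 to 0.06 range that the article gives for BP control.

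Assumed inputs: 25 patients per PHC-quarter (the article's BP-cohort size per PHC after attrition; adoption is measured on all attending adults), cluster autocorrelation (CAC) 0.8, and adoption of 60% under PF.

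For a paired contrast of PHC-quarter means, with s² the mean of p(1−p) over the two quarters:

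var = 2 × [ICC·s²·(1−CAC) + (1−ICC)·s²/m] / 30, referred to a noncentral t with 29 df (critical value 2.045).

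Example, 60% under PF against 45% in months 16-18:
- s² = (0.2400 + 0.2475)/2 = 0.24375
- var = 2 × [0.05 × 0.24375 × 0.2 + 0.95 × 0.24375/25]/30 = 2 × [0.0024375 + 0.0092625]/30 = 0.00078
- SE = 0.0279, and −0.15/0.0279 = −5.37

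Probability of a significant decline:

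| Adoption: PF months 10-12 / months 13-15 / months 16-18 | Planned: 16-18 vs 13-15 | Proposed: 16-18 vs PF 10-12 |
|---|---|---|
| 60 / 45 / 45 | 0 points, 2.5% | −15 points, 99.9% |
| 60 / 50 / 50 | 0 points, 2.5% | −10 points, 93.2% |
| 60 / 54 / 48 | −6 points, 53.8% | −12 points, 98.5% |

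The 2.5% is one tail of a 5% test under a true difference of zero. It holds whatever the ICC, autocorrelation or cluster size. The right-hand column does depend on them: for the 15-point loss it runs from 86% to 100% over ICC 0.01 to 0.10, autocorrelation 0.5 to 0.8 and 10 to 75 patients per PHC-quarter.

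**Simulation check.** 4000 trials per setting, logit-normal PHC effects, ICC 0.03, autocorrelation 0.8, 25 or 75 patients per PHC-quarter, and a paired test on empirical logits standing in for the GLMM. Immediate lasting losses of 15 to 25 points were flagged by the planned contrast in 2.1% to 2.9% of trials, against 2.4% to 2.7% with no loss at all. Comparing the pooled post-PF quarters with the last PF quarter flagged them in about 100%. With 65% falling to 40% and then recovering to 42%, the planned contrast flagged decline in 0.1% to 0.4%.

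**With calendar time in the model.** Adding quarter effects under the same inputs and assumed 3-month steps (Figure 2 is not available), the SE of the proposed contrast rises from about 2.8 to between 3.3 and 3.6 points. The range reflects one to three usual-care quarters before the first step, and PF quarters either pooled or separate. Power for a 10-point loss falls from 93% to about 76% to 83%. For a 15-point loss it stays near 98% to 99%. A contrast of months 16-18 with usual care has an SE of about 5 to 7 points.

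**The case against.** The strongest reply is that the plan does compare follow-up with the PF period. Rates are reported overall, by clinic and over time, and interviews with nurses and clinic leadership take place at 18 months. A fall from 60% to 45% would be visible beside the time effect. This stands. A reader might infer that a collapse would go unseen, and the article does not support that.

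A reader might also infer that a null time effect will be taken as proof of maintenance. The article gives a reading rule only for a negative effect. A null result would be consistent with its hypothesis, but nothing says that it establishes it.

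Third, exact contrasts are often left to a statistical analysis plan, and the article does not state how time is coded. This carries less weight. The article itself confines the outcome to the two follow-up intervals and assigns the PF comparison to descriptive summaries, so it states a choice and does not merely omit a detail.

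Fourth, the end of PF is not randomised separately. It follows PF start by 12 months at every PHC, so PF versus post-PF is a within-site comparison exposed to temporal trends. That is a real limit on the proposed contrast. It argues for a calendar-time-adjusted estimate with an interval over unadjusted summaries.

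Finally, the abstract sentence is a summary of what RE-AIM guides. The Study design section states the working aim as evaluating the sustainability of TASSH within the PHCs. The abstract alone does not bind the authors to a formal PF effect on sustainability, and the point does not rest on it.

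**Conclusion.** The concern holds in a limited form. The formal analysis of sustainability does not match the article's own definition: it tests drift within follow-up, while the definition asks whether adoption was maintained to 18 months. Loss at the withdrawal of PF would be described but not estimated or tested. That the planned contrast is blind to an immediate, lasting loss follows from its structure and needs no assumption. For a steady fall of 60%, 54%, 48% it sees 6 of the 12 points lost.

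The power figures for the alternative rest on an assumed ICC for adoption, autocorrelation, adoption level and 25 patients per PHC-quarter. The paired versions are somewhat optimistic because they ignore calendar time.

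Severity is should-fix. Sustainability is one of three secondary outcomes, and the primary analysis, randomisation, sample size and data collection are unaffected.

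**What to change.** In the Sustainability paragraph of the secondary analyses:

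1. Make the main sustainability analysis the contrast of months 16-18 after PF start with PF months 10-12, reported as an estimate with 95% CI and a test. Obtain it from the PHC-level GLMM by adding a post-PF state to the treatment factor, separating the PF and post-PF quarters, and keeping calendar time in the model.
2. Keep the comparison of months 13-15 with months 16-18 as a description of further drift.
3. State that a non-significant result will not be read as proof of maintenance; the interval shows how large a loss remains compatible with the data.
4. If a contrast of months 16-18 with usual care is wanted, label it exploratory and model-dependent. Few or no PHCs will still be in usual care by then. With five cohorts at assumed 3-month steps, the last cohort starts PF 12 months after the first, before the first cohort reaches its months 16-18.

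The cost is wording and some modelling. The Primary outcome section already has adoption collected monthly to the end of follow-up. The contrast should be fixed before outcome data are examined. The downside is that the PF to post-PF contrast is not separately randomised, depends on the calendar-time adjustment, and has somewhat less power than the paired figures suggest.

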**Fig. 1 Fig1:**
[figure not shown]
Overview of i-PARiHS and RE-AIM

The pre-implementation phase used the i-PARiHS in inquiring about the existing health system and PHC context to inform the development of a context-specific PF strategy. We assessed barriers and facilitators of integrating TASSH into PHCs for hypertension management through structured facility assessments and in-depth interviews with stakeholders within the PHCs and primary health system in Akwa Ibom. A pilot study was conducted during the pre-implementation phase wherein the feasibility of TASSH plus PF intervention was assessed in two PHCs. The facilities included in the pilot are not participating in the implementation phase.

In the implementation phase, we are using a SW-CRT design to introduce PF at the PHCs. The 30 PHCs were randomly allocated into five cohorts of six PHCs, and all begin in the TASSH only condition, which serves as the usual care control. Figure 2 overviews the stepped wedge design for this study. Given the SW-CRT, the length of time in TASSH alone (without PF) will vary, with a minimum duration of 3 months for the first cohort. Three months prior to the TASSH plus PF experimental condition starting, each cohort will have a training period. During this period, nurses and other staff at the PHCs receive training (or retraining) in delivering TASSH. Once the 3-month training period is completed, the PHCs will participate in a 12-month implementation period during which PF will occur.

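### Sustainability is defined as adoption maintained at 18 months, but the only model covers change within the six months after facilitation ends; the comparison with adoption under facilitation is descriptive only

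*Protocol article*

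**What the plan says.** The Secondary outcomes section gives the definition: "Sustainability is defined as the maintenance of TASSH adoption at HIV clinics at 18 months". The Study design section fixes the timing. PF lasts a year ("the PHCs will participate in a 12-month implementation period during which PF will occur"), and then: "Six months into this post-implementation period (18 months following the start of PF), we will evaluate the sustainability of TASSH within the PHCs".

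The Sustainability paragraph under Secondary outcomes analyses sets out the analysis:

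- The outcome is defined as for adoption and is "classified using two 3-month intervals during the follow-up measurement period lasting 6 months".
- Rates are described overall and by clinic, with tables over time.
- The link to the PF period is one sentence: "We will compare sustainability of TASSH to adoption in the intervention interval through descriptive summaries across sites".
- Change over time gets a GLMM: "Specifying a main effect of time with sustainability as our outcome", and "we will interpret a main effect of negative magnitude to indicate that rates of sustainability decrease over time".
- The hypothesis is: "We hypothesize that sustainability will not decline over time".

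Secondary hypotheses are tested at the two-sided 5% level (Power and sample size justification). Interviews with nurses and clinic leadership at 18 months add qualitative evidence (Secondary outcomes).

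**The concern.** To say that adoption was maintained, one needs the level it is maintained from. Here that is adoption while PF was running, most naturally its last quarter. The modelled outcome exists only after PF has ended, so the modelled time effect lies wholly inside follow-up. The primary analysis separately models time across the four PF quarters. Neither time model, as described, crosses month 12, which is when support is withdrawn and a loss is most plausible.

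The formal hypothesis therefore addresses whether adoption keeps falling after support has gone. The definition asks whether adoption held up when support went. The two can disagree: a center could lose much of its gain at month 12, stay flat, and be fully consistent with the hypothesis of no decline. Sustainability is one of the trial's stated aims and bears on the scale-up argument in the Implications section, so the quantity that matches the definition should carry an estimate and its uncertainty.

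**Working it through.** **Which months are compared.** PF covers months 1–12, and the Primary outcomes analyses section names its last quarter as months 10–12. Follow-up is 6 months in two 3-month intervals. The intervals are then 12 + 1 to 12 + 3 = months 13–15, and 12 + 4 to 12 + 6 = months 16–18. These month numbers are derived, not printed; they agree with the 18-month evaluation point.

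**What each comparison estimates.** Write A for adoption in months 10–12, B for months 13–15 and C for months 16–18.

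- Modelled time effect: C − B.
- Quantity matching the definition: C − A = (B − A) + (C − B).

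The step B − A, the change at withdrawal, does not enter the model. If adoption falls at once and then stays flat, C − B = 0 whatever the size of B − A.

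**Size.** The article gives no power, sample size or margin for sustainability, so there is no figure to reproduce. As an illustration, 4000 trials per scenario were simulated with 30 centers (from the article), 25 records per center and interval (the article's m for individual-level outcomes, borrowed here), and logistic random intercepts with ICC 0.03 (the middle row of Table 2). The adoption rates are assumed. The test was a center-level paired t-test, flagging decline when t < −2.045 (29 df, two-sided 5%). The contrast with PF used the mean of B and C against A.

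| A → B, C | Fall from A to C (points) | Flagged by C − B | Flagged by contrast with PF |
|---|---|---|---|
| 65% → 50%, 50% | 15 | 2.4% | about 100% |
| 65% → 45%, 45% | 20 | 2.6% | about 100% |
| 60% → 40%, 40% | 20 | 2.5% | about 100% |
| 65% → 50%, 45% | 20 | 46% | about 100% |
| 65% → 65%, 50% | 15 | about 100% | 91% |

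In the first three rows the 2.4–2.6% is just the lower-tail error rate of a two-sided 5% test. More records would not raise it, because the true C − B is zero. In the last row the planned test works well, so the blind spot is specifically a loss at withdrawal.

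**Approximate check of the contrast proposed below (C − A), first row.** Pairing within centers roughly cancels the random intercept. Variance per center ≈ 0.65 × 0.35/25 + 0.50 × 0.50/25 = 0.0091 + 0.0100 = 0.0191. Standard error ≈ √(0.0191/30) = 0.0252. The 15-point fall is 0.15/0.0252 ≈ 5.9 standard errors, and the 95% half-width is about 2.045 × 0.0252 = 0.052, or 5 points.

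Both calculations omit center-by-interval variation and adjustment for calendar time. Either would widen the interval, so the values near 100% are optimistic. They do not affect the finding about C − B.

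**The case against.** The strongest reply is that a reader might infer from this design that adoption which collapses when PF stops would be reported as sustained. The article does not support that. It plans to set follow-up beside the intervention interval, with rates by clinic and tables over time, and a 15- to 20-point fall would show there. The 18-month interviews are a further source. Nor does the article say that a null time effect proves maintenance, or that the model overrides the descriptive comparison. It says only that a negative effect will be read as a decrease. This stands, and it limits the point.

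It can also be said that the missing margin and the missing mention of a calendar-time term are details an article may leave to the full protocol or analysis plan. The Limitations section commits in general to adjusting for temporal trends. This stands too; neither is counted as a fault here.

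The coding of time in the model is not spelled out, so its restriction to follow-up is an inference. It is the natural one, because the outcome is classified only in the two follow-up intervals. And the modelled question, whether adoption erodes after support ends, is legitimate.

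What the reply does not remove is a stated choice: the comparison that matches the definition is assigned to description, while the model and the hypothesis are assigned to something else. That is not a detail left for later.

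**Conclusion.** The point holds in this form. The modelled analysis of sustainability does not estimate the quantity the article defines. It cannot detect a loss that happens when PF stops and then levels off: under the assumed rates, a fall of 15 to 20 points is flagged in about 2.5% of trials. The comparison that would address maintenance is planned, and would display such a fall, but has no stated interval or test. The formal hypothesis could therefore be upheld beside a descriptive table that contradicts it, and the article does not say how the two would be reconciled.

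The conclusion rests on reading the time effect as confined to the two post-PF intervals. The percentages also rest on the assumed rates, ICC and record counts; adoption uses aggregate data on all eligible patients, so actual counts may differ. This should be fixed. It is not critical, because the outcome is secondary and the analyses of adoption under PF and of BP control are unaffected.

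**What to change.** Make the main sustainability estimate a GLMM contrast of the last follow-up interval (months 16–18) with the last PF interval (months 10–12), and report months 13–15 against months 10–12 as well. One way is to extend the primary adoption model, keeping its calendar-interval effects and center random effects and giving condition separate levels for usual care, the four PF quarters and the two post-PF quarters. Report each contrast with a 95% confidence interval.

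Keep the within-follow-up time effect as a supporting analysis, and state that a non-significant effect will not be taken as evidence of maintenance. An acceptable-loss margin is optional; if one is used, set it before follow-up data are seen.

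The cost is analysis-plan wording. Adoption is already collected monthly through the end of follow-up (Primary outcome), so no new data are needed. The drawback is that the interval may be wide, especially after calendar-time adjustment, and the result may be inconclusive.
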